#### Assessment Procedures

After obtaining informed consent, the study staff conducted the baseline assessment interview. If the participant was unable to complete the interview on the same day, the interview was scheduled within 1 week and can be completed in person, through a secure video platform, or over the phone. The assessment consisted of a staff-administered interview and self-administered surveys and took approximately 1.5 hours to complete. Study data were collected and organized using Research Electronic Data Capture (REDCap) tools, which are hosted at Washington State University [19]. One exception was the Suicide Attempt Self-Injury (SASI), which was collected by interview, recorded on paper, reviewed, and then entered electronically after a study visit.

#### Randomization

Randomization to the intervention group or the treatment-as-usual (TAU) control group occurred after the baseline assessment had been completed. A biostatistician not involved with data collection programmed the randomization module in REDCap to enable site coordinators to access the assignment for each participant in real time. Randomization was stratified by site. To prevent bias that might arise when study coordinators intentionally or unintentionally anticipate an upcoming randomization assignment, assignments were blocked in randomly patterned groups of 2, 4, or 6, with assignments for each arm distributed evenly within each block. Follow-up interviews for the SASI were completed by staff blinded to the participants’ treatment allocation.

### Treatment Groups

#### Resources for All Participants

Study staff provided a “care card” to all participants at baseline, which detailed clinic contact information, business hours, and provided a list of local resources for mental health and traditional healing. This care card was developed in collaboration with behavioral and primary care staff at the clinics to ensure inclusion of appropriate resources. To protect patient privacy, the care cards did not mention the research study. Participants in both groups also received text messages to verify contact details at 6 months and to remind them of and confirm their 12-month follow-up interview.

#### Treatment as Usual

All participants in the study, regardless of their assigned treatment group, continued to receive the standard treatment normally provided by the clinic, including mental health services, medication management, substance abuse treatment, and case management. Data about the type and frequency of clinic visits by study participants during the study enrollment period were collected by the study team from the participants’ EHR after their study completion.

#### Caring Texts Intervention

In addition to receiving TAU, participants assigned to the caring texts intervention group also received 28-30 supportive and nondemanding text messages; examples of these messages are available in Table 1, and the complete schedule of messages is available in Multimedia Appendix 1. The number of messages sent depended on the date of enrollment, the participant’s birthday, anniversaries, holidays, and seasonal and local events. These messages were sent over 12 months, namely, daily for the first 3 days, then 6 weekly messages, 6 biweekly messages, and 6-monthly messages. Other messages include a birthday message, a holiday message (in December), a harvest message (in November), messages acknowledging an anniversary of loss and an anniversary of hope, and 4 messages for seasonal events. The study tailored messages to reflect locally appropriate holidays, events, and celebrations, and used the local language for greetings [20]. The messages were delivered through a secure online platform, LifeWIRE (LifeWIRE Group), which was compliant with HIPAA, HiTech, and FDA regulations for electronic interactions. This platform tracked all communication, preprogrammed messages, and offered the option for individualized responses to be typed and stored for record-keeping purposes.

**Table 1 table1:** Sample messages for caring text messages sent to intervention participants by site.

Timing	FNCH^a^ message (Albuquerque)	OHC^b^ message (Rapid City)
First day after enrollment (#1)	It was nice meeting and talking with you yesterday, [displayname]^c^. You showed great courage. Thanks for trusting me. -<staff name>^d^	Hello [displayname], It was nice meeting and talking with you yesterday. You showed great courage. Thanks for trusting me. -<staff name>
Weekly (#6)	Ya’at’eeh! Keshi! Guw’aadzi! No matter how you say “hello,” everyone is welcome at the FNCH Traditional Wellness Program. Please call (XXX) XXX-XXXX for more information. - <staff name>	Aŋpétu wašté [displayname]! Sending you positive vibes. Creator has good things for you. Smudging is a good way to stay in touch with the Creator. - <staff name>
Biweekly (#11)	Diné Prayer: “In beauty I walk, with beauty before me, behind me, above me, around me. Today I will walk out, greet the sun and the stars, everything negative will leave me, nothing will hinder me” *-*<staff name>	“One of the things my parents taught me, and I’ll always be grateful for the gift, is to not ever let anybody else define me.” -Wilma Mankiller. I believe in you, [displayname]. -<staff name>
Monthly (#16)	[displayname], being alive is fighting: “Being Indian is a combination of things. It’s your blood. It’s your spirituality. And it’s fighting for the Indian people” –Winona LaDuke -<staff name>	[displayname], I believe that the future holds many good things for you. Crazy Horse shared this vision: “I see a time of Seven Generations when all the colors of mankind will gather under the Sacred Tree of Life and the whole earth will become One Circle again.”-<staff name>
Spring (#21)	Spring is a time for prayers to help corn grow. So much will come up to greet the sun daily. Today is a new day! -<staff name>	[displayname], the Thunder Beings return to the homeland. Spring is our time to welcome their return - we can pray and give thanks for the promise of rain. -<staff name>

^a^FNCH: First Nations Community Healthsource.

^b^OHC: Oyate Health Center.

^c^[displayname] indicates that the participant’s name was used here.

^d^<staff name> indicates that the site staff signed the message with their own name.

The intervention and study design were adapted to the cultural values and context of the participating communities (eg, type of messages and topics, number of messages, and schedule) [20]. To create messaging that appealed to young urban AIs, the study teams conducted focus groups and semistructured key informant interviews with AI individuals affected by suicide, and gathered input from staff in the clinic’s behavioral health and traditional wellness departments, the project’s youth representatives, and study staff. Participants were asked to brainstorm and review text messages for their cultural appropriateness and relevance to young urban AIs in their community. The messages were then carefully reviewed and adapted by staff from the clinic’s behavioral health and traditional wellness departments, and research staff to ensure that they were consistent with the ideals of the caring texts intervention (ie, brief, supportive, and nondemanding). The messages used familiar language and were sent by research staff who had conducted the participants’ baseline assessments to establish continuity and connection.

### Data and Safety Monitoring

Site and coordinating center staff monitored participant safety. To determine and address potential suicide risk during assessments, study staff administered the University of Washington Risk Assessment Protocol to participants immediately before and after baseline and follow-up assessments [21]. If this assessment indicated moderate or severe suicidal intentions, or if the assessor has other reasons to be concerned about risk, a site-specific crisis protocol is implemented to ensure the participant receives appropriate care from a trained clinician who can more thoroughly assess their level of risk and initiate appropriate next steps.

All adverse events are identified through assessments or through care text messages, then recorded in the REDCap database, which automatically sends email alerts to the team overseeing participant safety. The site leads ensure high-risk participants receive appropriate management and follow the crisis protocol, including referral and a warm hand-off to clinic staff or a crisis line. The National Institutes of Health required a Data Safety and Monitoring Board to meet twice a year and oversee recruitment, adverse events, and protocol violations. After each meeting, the board prepares a brief report with recommendations for protocol modifications. All adverse events are reported to the universities’ Institutional Review Boards and tribal review boards, in accordance with their policies.

### Measures

A summary of all measures used in the study is available in Table 2. Unless otherwise noted, measures were administered as a survey in REDCap.

**Table 2 table2:** Summary of outcome and measures used in the urban caring text study.

Type, topic, and domain			Scale or measure
**Primary outcomes: suicidal behaviors**			
	Suicidal ideation	Suicidal Ideation Questionnaire (SIQ-Junior)	
	Recent suicide attempts	Suicide Attempt Self-Injury Count Recent	
	Suicide-related hospitalizations	Youth Health Services Measure	
**Secondary outcomes: social connectedness**			
	Thwarted belonging, burdensomeness	Interpersonal Needs Questionnaire	
	Loneliness	Loneliness Scale from NIH^a^ Toolbox	
	Perceived rejection	Social Distress Scale	
	Objective frequency of socialization	Social Contact Questionnaire	
	Connection to community	Social Connection Venn Diagram Task	
**Potential covariates and relevant factors of interest**			
	Suicide risk	Acquired Capability for Suicide Scale and Exposure to Suicide Questionnaire	
	Stress and trauma	Breslau Post Traumatic Stress Disorder Screener, Ayers Coping Scale, and Historical Loss and Trauma Scale	
	Substance use	Addiction Severity Index, Native American Version	
	Indigenous identity	Oetting and Beauvais Orthogonal Ethnic Identification Scale	
	Overall psychological well-being	Kessler Psychological Distress Scale	
	Overall well-being	EQ-5D-5L^b^	
	Overall well-being and health care usage	Health Economics Analysis Questionnaire	

^a^NIH: National Institutes of Health.

^b^EQ-5D-5L: EuroQol 5-Dimension 5-Level.

#### Primary Outcomes

Our primary outcome of interest was suicidal behavior. While suicidal ideation is more common than suicide attempts or attempts requiring hospitalization, ideation is not necessarily a concrete event and can be more difficult to measure. For this reason, ideation, attempts, and suicide-related hospitalization were all selected to measure the same underlying risk construct. The Suicidal Ideation Questionnaire-Junior, which has been validated with AIAN individuals, measured the study’s primary outcome of suicidal ideation [22]. It consists of 15 items that evaluate thoughts of death, desire to be dead, and specific thoughts of self-harm. Scores range from 0 to 90, with scores above 32 indicating active suicidal ideation [23]. The “junior” version of the questionnaire was used to accommodate participants with lower reading levels.

The SASI count (lifetime and recent) assessed the primary outcome of suicide attempts [24]. It is a concise questionnaire that determines the first, most recent, and most severe suicide attempt or nonsuicidal self-injury. It assessed the date, method used, and intent to die (ie, clear intent to die, ambivalent intent, or no intent to die), the highest level of medical treatment received (ie, none, doctor or clinic visit, emergency room, or admission to a medical unit), and lethality of each event. The SASI also posed questions about the number of attempts for each of the 17 methods, specifying intent to die, medical treatment received, and lethality for each one. Intent to die and lethality were derived from the SASI interview [24]. A lifetime version of the instrument administered at the baseline assessment captured all historical suicide attempts or nonsuicidal self-injury. A recent version of the instrument assessed only those events that occurred in the past year, both at baseline and follow-up assessments. The adapted version of the SASI used in this study simplified the language, included methods commonly used in AIAN communities, and added an assessment of drug and alcohol use at the time of the self-injury. The SASI was administered via interview.

The primary outcome of suicide-related hospitalizations and health care encounters was measured via the Youth Health Services Measure [25]. The questionnaire collected information about the use of and satisfaction with inpatient and outpatient medical care, emergency room visits, and the use of traditional healing. It could be used to identify health care encounters related to suicidal ideation or behaviors.

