**Methods:**

This 2-arm, double-blinded, randomized controlled trial is being implemented at 2 clinical sites with large AI populations. Partnering with clinics in Albuquerque, New Mexico, and Rapid City, South Dakota, we are recruiting AI adults aged 18-34 years to participate in a caring text message study. During the baseline visit, participants complete several surveys and an interview with study staff to understand their history of suicidal behavior. After completion of the baseline visit, participants are randomized to receive the intervention—approximately 30 caring text messages—or treatment as usual. The text messaging platform selected for this study allows bidirectional messaging; while there is no expectation that participants respond, they can provide feedback or seek additional resources. Participants are followed up at 6 and 12 months postbaseline. At the final 12-month follow-up visit, they complete many of the same surveys and participate in an interview to ascertain suicidality since their initial visit. The primary outcomes of interest are suicide-related behaviors—suicidal ideation, suicide planning, suicide attempt, or thoughts and actions requiring hospitalization. Secondary outcomes include social connectedness and other measures of mental health. We will use an intention-to-treat analysis with logistic and linear regression to calculate odds ratios and risk differences (95% CIs) for binary and continuous outcomes.

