### Data Analysis

#### Analysis plan

We expect that individuals receiving the culturally tailored text messages will have better outcomes than those in the treatment-as-usual control arm. Chi-square and *t* tests will be used to compare the overall percentages (binary outcomes) and mean differences (continuous outcomes) between study arms. We will conduct a sensitivity analysis using logistic or linear regression to adjust for baseline factors that are imbalanced between the intervention and control arms. Results will be presented as risk ratios and risk differences for binary outcomes, extracted from logistic regression models using marginal standardization, with 95% CIs [44,45]. Primary analyses will use an intention-to-treat approach.

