#### Power and Sample Size

We plan to recruit 350 people across both sites. We assume the study will have 70% retention at 12 months, yielding an analytic sample of 240 people (120 per group). With this sample, we will have 80% power to detect a 16% difference (Risk Ratio=0.47) in suicidal ideation between intervention and TAU groups, assuming that 30% of the TAU group reports suicidal ideation at follow-up. We will also be able to detect an 11% difference (Risk Ratio=0.25) in suicide attempts if 15% of the TAU group participants attempt suicide within the 12-month follow-up. There is variability in the literature regarding what constitutes a clinically meaningful effect size for reductions in suicidality and the best means of measuring such an effect (eg, degree of suicidality, reported number of attempts, etc). Regardless, we are confident in our ability to recruit a sizeable analytic sample in a difficult-to-reach population.

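### Three primary outcomes are tested separately with no order, composite or success rule; if any one may be claimed, the false-positive risk is about 10% to 14%, not 5%

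*Protocol article*

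**What the plan says.** Table 2 places three measures under the primary outcomes, and the Primary Outcomes section gives each the same rank. The SIQ-Junior "measured the study’s primary outcome of suicidal ideation". For the second, "The SASI count (lifetime and recent) assessed the primary outcome of suicide attempts". For the third, "The primary outcome of suicide-related hospitalizations and health care encounters was measured via the Youth Health Services Measure". The reason given for having three is that "ideation, attempts, and suicide-related hospitalization were all selected to measure the same underlying risk construct".

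Under Analysis plan, chi-square and t tests "will be used to compare the overall percentages (binary outcomes) and mean differences (continuous outcomes) between study arms". Results carry 95% CIs. No significance level, order or rule for combining the three outcomes is stated.

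Power and Sample Size treats two of the three separately. With 120 per group there is 80% power for a 16-point difference in ideation (risk ratio 0.47) from a control rate of 30%. Then: "We will also be able to detect an 11% difference (Risk Ratio=0.25) in suicide attempts", from a control rate of 15%. Hospitalization has no power figure.

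The abstract's list of primary outcomes differs: "suicidal ideation, suicide planning, suicide attempt, or thoughts and actions requiring hospitalization". Planning has no measure in Table 2 or in the Measures text.

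**The concern.** Three outcomes that each carry the label primary, each with its own test, give three chances at a positive trial. The article says that they reflect one construct, and its Principal Findings section anticipates reduced suicidality as a single primary result. A significant finding on any one could therefore be presented as confirming the hypothesis, and nothing in the text says whether that would be legitimate.

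Two things are at stake. The confirmatory claim has no defined error rate. And the ranking of the three outcomes stays open, although their names and instruments are published. The abstract reports that one site had finished follow-up by June 2025, so the time to settle this is limited.

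**Working it through.** **Inputs.** From Power and Sample Size: 120 per arm, 80% power, control rates 30% and 15%, differences 16 and 11 points, risk ratios 0.47 and 0.25. From Primary Outcomes: three primary outcomes. Assumed, because not stated: the test level, the correlations between test statistics, and the hospitalization rate.

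**Step 1: reproduce the stated power.** With p̄ = (p1 + p2)/2 and d = p1 − p2, the uncorrected size per arm is

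n = [z(1−α/2)·√(2p̄(1−p̄)) + z(0.80)·√(p1(1−p1) + p2(1−p2))]² / d²,

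and the continuity-corrected size is n′ = (n/4)·[1 + √(1 + 4/(n·d))]².

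- Ideation, 30% vs 14%, α = 0.05: n = (1.960 × 0.5858 + 0.8416 × 0.5748)² / 0.0256 = 104.0, so n′ = 116.2.
- Attempts, 15% vs 3.75% (risk ratio 0.25), α = 0.05: n = (1.960 × 0.4122 + 0.8416 × 0.4045)² / 0.01266 = 104.2, so n′ = 121.3.

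Both are close to 120. At exactly 120 per arm, corrected power is 81.4% and 79.5%.

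**Step 2: which level fits best?** Differences detectable with 80% power at 120 per arm. The arcsine rows use h = [z(1−α/2) + z(0.80)]/√60 and p2 = sin²(arcsin√p1 − h/2).

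| Level per outcome | Method | Ideation: points, RR | Attempts: points, RR |
|---|---|---|---|
| Stated | – | 16, 0.47 | 11, 0.25 |
| 0.05 | corrected | 15.8, 0.475 | 11.3, 0.247 |
| 0.05 | uncorrected | 15.0, 0.499 | 10.6, 0.291 |
| 0.025 | arcsine | 16.2, 0.460 | 11.1, 0.260 |
| 0.025 | uncorrected | 16.35, 0.455 | 11.5, 0.235 |
| 0.025 | corrected | 17.1, 0.431 | 12.1, 0.192 |
| 0.0167 | arcsine | 16.9, 0.438 | 11.5, 0.235 |
| 0.0167 | uncorrected | 17.1, 0.431 | 11.9, 0.206 |
| 0.0167 | corrected | 17.8, 0.408 | 12.6, 0.164 |

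The corrected calculation at 0.05 lies closest to both stated risk ratios. Fisher's exact test at 0.05 also gives about 80% (82.1% and 81.9%). A split over the two powered outcomes comes near but misses the risk ratios. A split over all three does not fit by any of these methods.

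**Step 3: familywise error if any one success counts.** Three independent tests at 0.05: 1 − 0.95³ = 0.143. For equally correlated normal test statistics, by simulation with one million draws:

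| Correlation | 0 | 0.3 | 0.5 | 0.7 | 0.8 | 0.9 |
|---|---|---|---|---|---|---|
| Familywise error | 14.3% | 13.7% | 12.6% | 10.9% | 9.8% | 8.3% |

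Counting only false claims of benefit, the independent case is 1 − 0.975³ = 7.3% against 2.5%.

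As a check, I simulated binary outcomes at 120 per arm (30%, 15% and an assumed 5% or 10% for hospitalization; correlation between the underlying normal variables 0 to 0.9). Uncorrected chi-square tests gave roughly 12% to 15%. Continuity-corrected chi-square tests, which reject less often than their nominal level, gave about 8% to 9%.

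**Step 4: what a late Bonferroni split would cost.** At 0.05/3 = 0.0167, power falls to about 67% for ideation and 62% to 65% for attempts with the correction (attempts at 4% or 3.75%), or about 73% and 70% to 73% without it. Restoring 80% with the correction needs 152 per arm for 30% vs 14% and 157 for 15% vs 3.75%.

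**The case against.** The strongest objection is that this is silence, not error: a multiplicity procedure and a success rule often sit in an analysis plan, which is not shown here. The article never says that there is no adjustment, nor that one positive outcome is enough. Powering each outcome at 0.05 is compatible with a fixed sequence or an all-must-succeed rule written elsewhere. The Primary Outcomes section also opens in the singular, with suicidal behavior as the outcome, which could point to a composite.

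Much of this stands, and it limits the conclusion. A reader might infer that the trial's error rate simply is two to three times 5%. The article does not support that, because the inflation depends on a success rule that it does not state. A reader might also infer that the power figures can arise only from an unadjusted 0.05. They fit that best, but the level and the correction are both unstated, and a two-way split by the arcsine method comes near. Nor does the abstract's list establish a fourth test: planning has no instrument, so no error figure for four tests is warranted.

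What does not stand is that nothing is fixed. The article assigns primary status three times over, describes separate comparisons, and publishes power figures that match no three-way split. Those statements have to be reconciled with whatever rule exists. An unseen plan would not remove the published mismatch between abstract and Methods.

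**Conclusion.** The point holds conditionally. As published, three primary outcomes are tested separately with no order, composite or success rule, and the power statement most plausibly gives each powered outcome the full two-sided 0.05. If a significant result on any one may be claimed as success, the chance of a false-positive primary claim is about 14% for independent tests and 10% to 13% at correlations of 0.5 to 0.8, instead of 5%.

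This rests on an inferred 0.05 level, on assumed correlations, and on tests that hold their nominal level; continuity-corrected tests in the analysis itself would give a smaller excess. A composite, or a rule that all three must succeed, would remove the inflation. The planning mismatch is a separate and minor contradiction.

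**What to change.** Before arm-level results are seen, state one rule. For example: the primary outcomes are tested in a fixed order at two-sided 0.05, namely SIQ-Junior ideation, then SASI attempts, then suicide-related hospitalization; each later outcome is confirmatory only if all earlier ones are significant.

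This order keeps the stated ideation power, but it is not the only acceptable one. The article itself notes that ideation is harder to measure than a concrete event, and the investigators may prefer another pre-set order, which controls error equally well.

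The change is wording only. The downside is that later outcomes cannot be claimed confirmatorily if an earlier one fails. In the example order, the chance of confirming both ideation and attempts, if the two tests were independent, is 0.814 × 0.795 = 0.65 under the planning assumptions. Positive correlation would raise it, to at most 0.795.

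Separately, bring the abstract into line with the Methods: remove suicide planning from the primary outcomes, or label it exploratory and name its source item.

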Patients—referred to as “relatives” by local staff, which underscores their shared heritage—receiving care at OHC complete routine depression screening as part of most health care encounters. Individuals who report moderate levels of depression or mild, moderate, or severe risk for suicide were referred to behavioral health. The behavioral health provider could offer treatment or referral for services. The relative was informed about the present study. If they were eligible and interested, their contact information was shared with research staff, who are not OHC employees. Study staff follow up with OHC referrals and invite relatives (patients) to participate in the study. Study staff scheduled a time to complete informed consent and the baseline interview.

While the text message intervention contacted participants in the treatment group, responses were unnecessary unless scheduled, requested, or activated by an immediate crisis. However, participants frequently respond to the scheduled messages, usually expressing gratitude or mild distress. To maintain contact and maximize retention, participants in the control group and the treatment group were contacted by the study team at 6 months postbaseline assessment to confirm their contact information. Ten months after enrollment, site staff were permitted to begin contacting participants to schedule or confirm the 12-month follow-up assessment. Participants received text messages (email or private messaging for those who can no longer use text messaging) asking them to confirm the follow-up assessment appointment. If site staff do not receive a response, they contact the alternate contact provided by all participants at the baseline assessment to try and ascertain updated contact information. If a participant does not respond to the reminders and misses their scheduled appointment, the site staff will continue to try and contact them for up to 6 months after their due date, unless they decline further contact. Eighteen months after enrollment, participants were considered lost to follow-up.

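### The follow-up SASI asks only about the past year, but the 12-month visit may run to month 18, so the attempt outcome covers different periods for different participants

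*Protocol article*

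**What the plan says.** Four places in the protocol article fix the period over which attempts are counted.

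- **Primary Outcomes**, on the SASI: "A recent version of the instrument assessed only those events that occurred in the past year, both at baseline and follow-up assessments". The lifetime version is described for baseline only.
- **Recruitment and Retention**, on a participant who misses the 12-month appointment: "the site staff will continue to try and contact them for up to 6 months after their due date". It then adds: "Eighteen months after enrollment, participants were considered lost to follow-up".
- **Power and Sample Size** states the attempt risk for treatment as usual (TAU) as a 12-month quantity: "if 15% of the TAU group participants attempt suicide within the 12-month follow-up".
- **Abstract, Methods**, on the final visit: participants "participate in an interview to ascertain suicidality since their initial visit".

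The Analysis plan compares simple percentages between arms by chi-square, and the Missing Data section makes the complete-case analysis primary. A participant interviewed late is a complete case, and neither section adjusts for when the interview took place.

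**The concern.** A past-year recall and a recall since the initial visit are the same only when the interview is held 12 months after baseline. For later interviews the past-year window slides forward: early follow-up is not asked about, and time after the end of the 12-month intervention is included. The outcome in the power statement is an attempt in the first 12 months, and for late attenders the instrument does not measure that.

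Two things are at stake. The attempt outcome mixes different periods across participants, so the reported risk difference has no single time frame. And if the messages work mainly while they are being sent, replacing intervention months with later months pulls the arms together. The protocol plans attempts on 120 per group and a large detectable difference, so there is little room for dilution.

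**Working it through.** **Inputs from the protocol.** Recall of 12 months back from the interview; contact attempts to month 18; TAU attempt risk 15%; detectable risk ratio 0.25; 120 per group; core messages 3 daily, 6 weekly, 6 biweekly and 6 monthly (Caring Texts Intervention).

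**Assumed, not in the protocol.** Two-sided 5% level; constant attempt hazard; true effect close to the planned detectable effect; no effect after month 12; and the share of late visits, shown as a range.

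**1. The plan's own power.** The protocol states "we will have 80% power to detect a 16% difference (Risk Ratio=0.47) in suicidal ideation" and that it can "detect an 11% difference (Risk Ratio=0.25) in suicide attempts". With the two-proportion formula and continuity correction:

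- Ideation, 30% v 14%: 117 per arm needed; power at 120 is 81.4%.
- Attempts, 15% v 3.75%: 122 per arm needed; power at 120 is 79.5%.

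The stated power therefore reproduces and is not in dispute.

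**2. The window.** An interview at month L covers months L − 12 to L. Core messages are laid out on days 1 to 3, then weekly to day 45, biweekly to day 129, and monthly after that. The birthday, holiday, harvest, anniversary and seasonal messages are left out because their dates depend on the calendar.

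| Interview at month | Months asked about | Core messages sent in the unasked months (of 21) |
|---|---|---|
| 12 | 0–12 | 0 |
| 13 | 1–13 | 6 |
| 14 | 2–14 | 10 |
| 15 | 3–15 | 12 |
| 16 | 4–16 | 14 |
| 17 | 5–17 | 15 |
| 18 | 6–18 | 16 |

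**3. Effect on one month-18 interview.**

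- TAU cumulative hazard over 12 months: −ln(1 − 0.15) = 0.1625.
- Intervention with hazard ratio 0.27 (about 4%/15%): 0.27 × 0.1625 = 0.0439, a 12-month risk of 1 − exp(−0.0439) = 4.3%. Difference: 15.0 − 4.3 = 10.7 points.
- Months 6–18 with no effect after month 12: 0.0439/2 + 0.1625/2 = 0.1032, a risk of 1 − exp(−0.1032) = 9.8%. TAU stays at 15%. Difference: 15.0 − 9.8 = 5.2 points.
- If the effect instead persists unchanged to month 18, the cumulative hazard over months 6–18 is again 0.0439, the risk is 4.3%, and nothing is diluted.

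**4. Effect on the trial.** This step uses a rounded intervention risk of 4%. A past-year recall then records 1 − exp(−(0.75 × 0.0408 + 0.25 × 0.1625)) = 6.9% at month 15, and 1 − exp(−(0.5 × 0.0408 + 0.5 × 0.1625)) = 9.7% at month 18, where 0.0408 = −ln(0.96). If a share f of analysed participants attends late, the recorded intervention risk is p = (1 − f) × 4% + f × (late risk). Power at 120 per arm, without continuity correction, is Φ((d − 1.96·SE0)/SE1), where d = 0.15 − p, SE0 is the pooled and SE1 the unpooled standard error.

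Example, f = 30% at month 18: p = 0.7 × 4% + 0.3 × 9.67% = 5.7%; d = 0.093; SE0 = 0.0393; SE1 = 0.0389; power = Φ(0.41) = 66%.

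| Share late | All late visits at month 15 | All late visits at month 18 |
|---|---|---|
| 0% | 83% | 83% |
| 10% | 81% | 78% |
| 20% | 78% | 72% |
| 30% | 75% | 66% |

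The starting value is 83% because this step uses 4% and no correction; with the correction, 15% v 4% has power 77.0%. The fall across the table is what matters.

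**5. The other reading.** If the Abstract's wording governs, a month-18 attender reports 18 months of events while an on-time attender reports 12. The TAU risk for that person becomes 1 − 0.85^1.5 = 21.6% instead of 15%. Neither reading gives everyone months 0–12.

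**The case against.** The interview form is not shown. In a condensed article, a past-year recall may be shorthand for a nominal 12-month visit, and the Abstract's wording points that way. That lowers certainty about the prompt in use, but the Primary Outcomes text is the specific description of the instrument and says only past-year events were assessed. On either reading the window is not common to all participants, so the sections need reconciling.

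Part of the problem can be handled in the analysis, and those rules may sit in a statistical analysis plan that is not shown. The SASI dates the first, most recent and most severe events, so many events after day 365 can be removed. This stands. It does not recover attempts in early months that a late attender was never asked about.

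The large figures are also extreme. The 5.2-point result applies only to interviews at month 18 with no carry-over, and a persisting effect would shrink or remove the dilution. This stands too, and the size below is stated accordingly.

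A reader might infer three stronger things that the documents do not support:

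- **Attempts before randomization are counted.** The month-10 provision concerns scheduling and confirming appointments. No section allows the visit itself before month 12.
- **Lateness differs by arm and biases the comparison.** Only the intervention arm gets regular messages, so this is conceivable. But both arms get the same 6-month contact and reminders, follow-up SASI interviewers are blinded, and nothing documents a difference. It is a conditional risk to check.
- **The densest message months are lost in general.** A month-13 interview misses 6 of 21 core messages; 16 are missed only at month 18.

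**Conclusion.** The point holds. As written, the attempt outcome covers months 0–12 only for participants interviewed at month 12. Each month of delay drops one month after randomization and adds one after month 12, and the primary complete-case comparison takes these interviews in unadjusted. A true effect may be diluted.

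The size cannot be fixed from the documents, because neither the share of late visits nor the persistence of the effect is given. Assuming constant hazards and no carry-over, the worst case is a fall from 10.7 to 5.2 points among month-18 visits. With 10% to 30% of analysed participants attending at month 15 to 18, power for attempts falls from about 83% to between 81% and 66%. With a fully persisting effect there is no dilution, but the mixed window remains. The finding concerns attempts only; no window problem is shown for ideation or hospitalization.

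**What to change.** 1. Reconcile the Abstract, Recruitment and Retention, Primary Outcomes, and Power and Sample Size so that they state one period for the attempt outcome.
2. Define the outcome as at least one attempt from randomization through day 365, and tabulate later events separately.
3. For interviews still to come, ask about all events since the participant's baseline date and record event dates. Both the Abstract and the Results section describe South Dakota as still enrolling, so this can still help.
4. For completed interviews, exclude events dated after day 365 and treat the unasked early months of late visits as missing, not as event-free. The per-method counts are not described as dated, so a rule is needed for undated events.
5. Report visit timing by arm and site, and add a sensitivity analysis limited to visits near month 12.

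**Cost.** One changed prompt, one derivation rule and one further analysis. Recall becomes somewhat longer for late visits, and completed and remaining interviews will have used different prompts. Because randomization is stratified by site and blocked in groups of 2, 4 or 6, that change should fall about equally on the two arms.
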